### Quality control

2.14

The reasons of dropouts or withdrawals throughout the treatment and follow-up periods will be fully recorded. To ensure trial quality, the quality monitors will verify all the process details at regular intervals and check the authenticity of the data. Moreover, a third party (CACMS) will be invited to manage the data independently.

Because differences among centers can cause bias, to reduce the bias, the evaluation of the rating scales in every subcenter will be executed by 2 psychiatrists who have been trained with the same criterion of evaluating. Also, there are 6 psychiatrists in total. All acupuncturists will receive special training about the study and manipulations including locations of acupoints, depth, and direction of needling, frequency of lifting and inserting, and so on before recruitment. To record the attendance and compliance, we make record cards for patients which cover date of treatment, personal information, and their signatures after every treatment.

## Discussion

3

Poststroke depression is a secondary neuropsychiatry disease, which is now considered its pathogenesis involving endogenous factors like neurochemical substances and inflammatory cytokines, and also exogenous factors like sex, age, marriage, social environment, education, life stress, and so on by reference to the primary depression.^[26]^ It is still unknown whether the pathogenesis is with particularity for PSD itself. Apart from this, the PSD diagnosis is confusion. The CCMD-III, ICD-10, and DSM-IV are the most commonly used in China.^[27]^ However, there was no clear diagnostic criterion for PSD above. DSM-IV categorizes PSD as “Mood disorder due to a general medical condition (ie, stroke),” with the specificities of depressive features, major depressive-like episodes, manic features, or mixed features. Refer to the diagnostic criteria of depressive episode in CCMD-III, ischemic stroke patients who were in depressed mood will be diagnosed with PSD. Therefore, according to patient symptoms combined with rating scale scores, we hope to obtain high-quality research data from this multicenter clinical trial that could provide reliable basis to future related study.

Fluoxetine hydrochloride, which is chosen as a standard drug therapy in this study, has been found to be effective and safe in PSD.^[28,29]^ A large number of ischemic stroke patients are recommended to take clopidogrel to prevent thrombosis.^[30]^ However, antidepressants might also increase the risk of drug-drug interactions. For example, SSRIs like fluoxetine and fluvoxamine are always avoided in ischemic heart disease patients who are receiving clopidogrel.^[31]^ Also, other studies have found that fluoxetine may potentially diminish the efficacy of clopidogrel.^[32]^ Moreover, the US Food and Drug Administration (FDA) reminded the public to avoid fluoxetine hydrochloride combination with clopidogrel because of the reasons above,^[33]^ especially for stroke patients. Hence, patients diagnosed with depression after ischemic stroke who were useing clopidogrel would not be recommended to take fluoxetine.^[34]^ For this, acupuncture on PSD may be a promising alternative therapy.

Acupuncture has been widely used and received in clinical practice in China.^[35]^ Patients in China are usually familiar with acupuncture, and expect to receive acupuncture treatments when they participate in this kind trial. Apart from this, because acupuncture is often regarded as an invasive operation,^[36]^ it is difficult to design a nonpenetrating sham acupuncture, which does not produce any physiological effects,^[37]^ and would not be experienced and recognized by patients at home. However, to improve subject compliance and achieve blinding, sham acupuncture will be necessary in the control group, whereas placebo pills will be adopted in experimental group in a high-quality RCT. So, in this study, sham acupuncture and placebo pills are applied simultaneously to eliminate the placebo effect. We choose needling at blunt acupoints as sham acupuncture without effect on depression, based on literatures^[18]^ and clinical experience.

Although studies have showed the efficacy of acupuncture for PSD,^[38,39]^ multicenter and large-sample RCTs are still lacking, and also the relevant mechanism research, which would be helpful to provide high-quality evidence for evaluation of acupuncture on PSD. Our protocol was designed through an extensive discussion by reference to several previous related studies.^[40–42]^ We try our best to attempt to minimize the biases that may influence study results. Finally, we intend to demonstrate the hypothesis that acupuncture as an alternative may be validated for PSD.

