## Introduction

1

Poststroke depression (PSD) is a serious and common complication of stroke.^[1]^ Reports revealed that the prevalence of PSD was from 30% to 65%.^[2,3]^ PSD has been associated negatively with survival, cost of medical care, and compliance with therapy including rehabilitation, functional outcome, resumption of social activities, and quality of life.^[4]^

At present, the treatment of PSD mostly applies selective serotonin reuptake inhibitors (SSRIs). A meta-analysis of randomized controlled trials for PSD has revealed that patients in the SSRIs group had make great improvement in depressive symptoms significantly compared with the placebo group.^[5]^ Several controlled studies have demonstrated that while some patients made improvement on depression scores significantly, others discontinued due to side effects.^[6,7]^ And SSRIs have slow onset speed about 3 to 4weeks.^[5]^ A trial suggested that the advantages of fluoxetine hydrochloride could not be demonstrated within the first 3 months compared with controlled treatment.^[8]^ On the contrary, the use of antidepressants might also increase the risk of interactions derived from various drugs, as most stroke patients concurrently take.^[9]^

Acupuncture is 1 of the main treatments of traditional Chinese medicine (TCM) which has been used for over 2000 years. Acupuncture is widely used in the treatment of PSD. A meta-analysis has demonstrated that the curative effect of acupuncture on PSD was superior to antidepressants among waitlist controls in improving both response and symptom severity.^[10]^ Another meta-analysis revealed that there is no difference in effective rate on comparison between the acupuncture group and western medicine group in treating PSD.^[11]^

In China, because of the good effect, more and more patients are willing to choose acupuncture for PSD. However, no sufficient clinical trial data and solid evidence could confirm whether acupuncture could yield certain efficiency in treating PSD and how acupuncture works. It is necessary to verify the effectiveness and mechanism of acupuncture from senior quality studies. Now, the evidence about acupuncture effect on treating PSD is inadequate and must apply further strictly design clinical studies.

The primary objectives of this study are to evaluate the efficacy and mechanism of acupuncture treatment and follow-up on PSD during 6 months.

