#### Inclusion criteria

2.3.1

The inclusion criteria are as follows:

1.Subjects diagnosed with ischemic stroke in International Classification of Diseases (ICD-10-I63.902).^[13]^2.Subjects diagnosed with secondary mild and moderate-grade depression, 17-item Hamilton Depression Scale (HAMD-17) scores between 7 and 24 points^[14]^, according to the Diagnostic and Statistical Manual of Mental Disorders-Fourth Edition (DSM-IV) or Chinese Classification and Diagnostic Criteria of Mental Disorders-Third Edition (CCMD-III).^[15,16]^3.Subjects aged between 40 and 80 years old, male or female.4.Subjects diagnosed with depression for the first time after ischemic stroke.5.Subjects diagnosed with initial PSD within 6 months.6.Cooperation during examination, without aphasia and severe cognitive disorders, Mini-Mental State Examination (MMSE) scores >17 points^[17]^.

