#### Exclusion criteria

2.3.2

The exclusion criteria are as follows:

1.Subjects diagnosed with primary depression or secondary major depressive disorder, HAMD-17 scores >24 points^[14]^.2.Participation in any other clinical trial or taking antidepressants in recent 2 weeks.3.With aphasia and severe cognitive dysfunction (MMSE scores <17 points).^[17]^4.With severe heart disease, malignancy, kidney, and liver function insufficiency.5.Pregnant or lactating women.

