### Interventions

2.7

Interventions were selected based on the theory of TCM and expert-level discussions. The acupuncturists involved have received their practitioners’ license from China's National Health and Family Planning Commission, who have worked for more than eight years. Subjects in experimental group received verum acunpuncture and placebo pills, and others in control group received sham-acupionts acunpuncture and medications. Apart from this, the regular drugs used in neurological department are allowed, such as antihypertensive drugs, lipid-regulating drugs, and antiplatelet drugs.

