##### Fluoxetine hydrochloride

2.7.2.2

Fluoxetine hydrochloride tablets (10 mg per tablet; Changzhou Siyao Pharmaceutical Co., Ltd., Changzhou, China) as a SSRI are used. Two tablets each time, one time a day for 12 weeks.

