### Randomization and blinding

2.12

After recruitment, the Central Randomization System performed by the China Academy of Chinese Medical Sciences (CACMS) would be used to randomize patients who meet the eligibility criteria into 2 groups at a ratio of 1:1. Every center will compete for the random numbers from random sequence generated by the Central Randomization System. Each subject will be registered with a unique ID. After the clinical screening and getting the informed consent forms, subjects will be assigned to experimental group (verum acupuncture + placebo pills) and control group (sham-acupoints acupuncture + fluoxetine) randomly. Each subject will receive the similar the number of acupoints and medications, as well as the stimulating amount of needling. Both groups will be in the package with the same looking and similar inner feeling, whereas all subjects will not be aware of the grouping.

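### The article advises against fluoxetine for depressed ischemic-stroke patients on clopidogrel, but its eligibility and concomitant-drug rules let such patients be randomised to fluoxetine

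*Protocol article*

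**What the plan says.** The Discussion (section 3) sets out an argument about drug interaction. Many ischemic-stroke patients are advised to take clopidogrel against thrombosis. Fluoxetine may weaken its effect. The US regulator has advised against the combination. The article then concludes that "patients diagnosed with depression after ischemic stroke who were useing clopidogrel would not be recommended to take fluoxetine" and presents acupuncture as an alternative for this reason. The Introduction has already warned that "the use of antidepressants might also increase the risk of interactions derived from various drugs, as most stroke patients concurrently take".

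The operational rules are these:

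- Inclusion criteria (2.3.1): "Subjects diagnosed with ischemic stroke in International Classification of Diseases", with a first depression after that stroke.
- Exclusion criteria (2.3.2): the only medication named is an antidepressant, in the words "taking antidepressants in recent 2 weeks".
- Interventions (2.7), for both groups: "the regular drugs used in neurological department are allowed, such as antihypertensive drugs, lipid-regulating drugs, and antiplatelet drugs".
- Randomization and blinding (2.12): "subjects will be assigned to experimental group (verum acupuncture + placebo pills) and control group (sham-acupoints acupuncture + fluoxetine) randomly", in a 1:1 ratio, and "all subjects will not be aware of the grouping".
- Fluoxetine hydrochloride (2.7.2.2): 10 mg tablets that "as a SSRI are used. Two tablets each time, one time a day for 12 weeks".

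**The concern.** The patients whom the Discussion says should not be recommended fluoxetine are the patients whom the trial recruits, apart from the clopidogrel use itself. The article uses the interaction as part of its reason for testing acupuncture, but does not carry it into the eligibility or concomitant-drug rules. The article does more than stay silent on interacting drugs: section 2.7 gives a positive permission for the class to which clopidogrel belongs.

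What is at stake is avoidable exposure. The harm that the article names is a possible loss of clopidogrel's protection against thrombosis, in people who have already had an ischemic stroke. The trial does monitor safety. Adverse events are recorded throughout, serious ones go to the principal investigator at once (2.8), neurological deficit is scored repeatedly (2.10), and adverse events are compared between groups (2.13.3). These measures find an event once it has happened. They do not prevent the exposure.

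**Working it through.** The check is one of consistency, so it consists of following one patient through the rules as written.

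| Step | Rule | Result for a clopidogrel user with depression after ischemic stroke |
|---|---|---|
| Entry | 2.3.1 | Can qualify: nothing in the criteria concerns antiplatelet treatment |
| Exclusion by drug | 2.3.2 | Not excluded: only recent antidepressants are named |
| Exclusion by illness | 2.3.2 | Not excluded as such: severe heart disease is listed, but the Discussion ties clopidogrel to ischemic stroke itself |
| Concomitant drugs | 2.7 | May continue: antiplatelet drugs are allowed, with no exception |
| Allocation | 2.12 | 1:1, so a 1 in 2 chance of fluoxetine |
| Comparison with the article's advice | 3 | The combination that the Discussion says is not recommended |

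No step stops this patient. The article gives no washout, switch or review rule for clopidogrel.

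**Dose and duration.** 2 tablets × 10 mg = 20 mg per day. 12 weeks × 7 = 84 days of possible combined use.

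**Number exposed.** The fluoxetine arm is planned at 104 patients (2.5). That is the size of the arm, not the number taking both drugs. The article says only that many ischemic-stroke patients are advised to take clopidogrel and gives no share, so no count can be derived.

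**How many could still be protected at entry.** Section 2.6 gives May 2016 to June 2018 for the study, and then expects follow-up to end in the second half of 2019 because recruitment was delayed. Treatment and follow-up take 12 + 12 = 24 weeks, or 24 × 7 = 168 days (2.1). Counting back from the end of the last patient's follow-up:

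- 1 July 2019 − 168 days = 14 January 2019
- 31 December 2019 − 168 days = 16 July 2019

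If randomisation comes directly before the 24 weeks, the last one falls between about mid-January and mid-July 2019, after the June 2018 date. The article does not say how many patients were still to be randomised when it was written.

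**The case against.** The strongest reply is that this is a condensed journal article. Section 2.7 describes concomitant drugs in one sentence, by class and by example, and does not name clopidogrel. The class includes drugs to which the Discussion does not object. Lists of prohibited drugs and contraindication checks at screening usually stand in the full protocol, which is not shown. This stands as a limit: the article cannot prove that no restriction exists. It does not remove the point, because the article states a permission without exception and contradicts it in its own Discussion.

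A second reply is that the Discussion is cited background and not a trial rule. Its wording on harm is cautious, and the same paragraph describes fluoxetine as effective and safe after stroke. The clinical weight of the interaction at this dose and duration rests on references that cannot be checked here. This also stands, and it lowers the severity. The general statement on safety does not answer the point, however, since the paragraph goes on to single out clopidogrel users.

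Third, few patients may remain to be randomised, so a change to eligibility alone may protect hardly anyone. That is correct, and it is why the fix must also reach patients already on study medication.

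A reader might infer more than the documents support:

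- That many patients did take both drugs. No share or count is given.
- That the trial authorises the combination outright. It allows a class, and a fuller document may narrow it.
- That safety monitoring is missing. It is described in 2.8, 2.10 and 2.13.3.
- That the HAMD-17 or SDS comparison is biased. The interaction described concerns clopidogrel's effect on thrombosis, and nothing in the article links it to the depression scores.

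**Conclusion.** The inconsistency is real and can be read from the article alone: its rules allow a combination that its Discussion says is not recommended for this population. A clopidogrel user who meets the criteria has a 1 in 2 chance of 20 mg fluoxetine daily for up to 84 days alongside clopidogrel. The number affected is unknown.

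The conclusion assumes that the article's rules are complete on this matter, which the full protocol could disprove. It takes the article's account of the interaction as given. It concerns patient safety only and does not touch the validity of the primary comparison. It deserves correction, but the cautious source, the unknown exposure and the late stage of recruitment keep it below the level of a defect that must be cured before the trial can go on.

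**What to change.** 1. **Patients still to be randomised.** Amend 2.3.2 and 2.7 so that current clopidogrel users are not enrolled unless their treating physician has already placed them on another antiplatelet drug. Apply the rule before randomisation and to both arms, which keeps the groups comparable and does not reveal the allocation.
2. **Patients now on study medication.** Review concomitant drugs promptly in both arms. The treating physician decides what to do for any clopidogrel user. If clopidogrel becomes necessary, for example after a recurrent stroke, stop the study medication and do not withhold clopidogrel. Keep the patient in follow-up and in the intention-to-treat analysis.
3. **Reporting.** Tabulate recurrent stroke and other vascular events by arm and clopidogrel use, as description only. Such a table cannot establish that the combination was safe, so it supplements steps 1 and 2 and does not replace them. The patient diary (2.10) tracks medications; whether it captures clopidogrel use at baseline is not stated, so clinical records should be checked as well.

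If the full protocol already restricts the combination, it is enough to state that rule in 2.7, complete the review in step 2 where it has not been done, and add the table.

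The cost is a short amendment, one medication review and one table. Recruitment may slow somewhat. The entry population changes late in the trial, and the results will not cover clopidogrel users, for whom the Discussion sees particular value in acupuncture.
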